**Methods:**

The Gore Together Aortic Registry is an international, prospective, observational registry initiated in response to increased regulatory emphasis on long-term post-market surveillance. This registry will enroll approximately 3,355 adult patients (≥18 years old) from over 170 global clinical centers, undergoing routine clinical care with GORE® aortic endovascular devices. Enrollment commenced based on standard clinical application, with data and imaging collection beginning at the time of hospitalization, and at each follow-up period.

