### Participants and enrollment

2.3

As a real-world registry and collaboration across academic and community centers, enrollment is structured to ensure comprehensive regional representation of diverse patient populations through a multi-site approach, encompassing 96 clinical centers for the EXCC/IBE module, 57centers for the CTAG-AC module, and 26 centers for the TBE module (Table 1). The total number of enrolled patients will vary by module. The EXCC/IBE module targets up to 2,000 patients (1,700 and 300, respectively), the CTAG-AC module aims to enroll 1,200 participants, and the TBE module includes approximately 155 subjects. Follow-up duration is tailored to the characteristics of the devices under investigation. The EXCC/IBE, and CTAG-AC modules follow patients for ten years post-procedure, whereas the TBE module has a follow-up period of two years. The duration of the latter was considered sufficient for assessing mid-term device performance, particularly in the context of evaluating regional variations in device utilization and procedural outcomes. This approach is supported by the existence of separate, ongoing longitudinal data collection efforts designed to capture long-term outcomes (9).

**Table 1 T1:** Together aortic registry enrollment.

Devices	Clinical Sites	Enrollment Target			Total
	Total No. of Sites^a^	North America	EMEA^b^	Asia Pacific^c^	
GORE® EXCLUDER® EXCC module	96	790	505	405	1,700
GORE® EXCLUDER® IBE Module		110	45	145	300
GORE® TAG® Conformable with Active Control Thoracic Stent Graft Module	55	600	300	300	1,200
GORE® TAG® Thoracic Branch Endoprosthesis (TBE) Module	26	–	120	35	155

a This is an approximate number as the site selection process is ongoing.

b Europe, Middle East and Asia region.

c Australia, Japan, New Zealand.

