### Minimum enrollment targets

2.8

Minimum enrollment targets for the EXCC/IBE modules were established based on an assumed outcome rate 10%, which is on the scale of expected endoleak (12). A small subset of 20% of all subjects (*n* = 600) represents both possible ad-hoc sub-analysis and a conservative estimate of subjects available at 10 years. With the full anticipated enrollment of 2,000 EXCC subjects, there is 80% power to detect a difference between 8.5% vs. 10% rates. For events with rarity of 1/350, there is greater than 80% probability to observe one or more among a small subset of 600 subjects and six or more events among the full 3,000 subjects. Among the full sample of 3,000 EXCC subjects, and an outcome with rate of 10%, a 95% confidence interval length would be 2.2% and among the reduced population of 600, the 95% confidence interval length would be 5.0%.

For the TA module, enrollment targets were derived assuming an outcome rate of 10%, which is on the scale of expected endoleak for this patient population (13). With respect to the anticipated overall registry of *N* = 1,200 subjects, a small subset of *n* = 120 (10%) represents both a possible *ad hoc* subgroup analysis sample as well as a conservative estimate of subjects available at 10 years. With an enrollment of *N* = 1,200, there is greater than 80% probability to observe one or more of an extremely rare events (1/700) and four or more of a rare event (1/200). This enrollment target supports population proportion estimation with exact confidence interval width of, for example, 3.5% for *P* = 10%, or a maximum of 5.7% for *P* = 50%. For subgroup analyses composed of 10% of the registry (*N* = 120), the exact confidence interval widths would be 11.5% for *P* = 10% and 18.5% for *P* = 50%.

Lastly, for the TB module, the minimum enrollment determination was based on detecting rare events and reasonable confidence interval widths for binomial proportion estimates applied to either the overall population or to subgroups. With an enrollment of *N* = 155, there is greater than 80% probability to observe one or more unusual (1/90) and four or more uncommon events (1/25). This enrollment target supports population proportion estimation with exact confidence interval width of, for example, 6.9% for *P* = 4%, or a maximum of 16.3% for *P* = 50%.

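### Section 2.8 calls 2,000 the full EXCC/IBE enrolment but computes its rare-event and interval figures for 3,000 and a 20% subset of 600; at 2,000 the six-or-more claim fails and the intervals are longer

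*Protocol article*

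**What the plan says.** Section 2.8 (Minimum enrollment targets) gives two sizes for the same module. The power sentence uses 2,000: "With the full anticipated enrollment of 2,000 EXCC subjects, there is 80% power to detect a difference between 8.5% vs. 10% rates". The precision sentence uses 3,000: "Among the full sample of 3,000 EXCC subjects, and an outcome with rate of 10%, a 95% confidence interval length would be 2.2" per cent, followed by a length of 5.0% for 600 subjects. The rare-event sentence, for a rate of 1/350, says "there is greater than 80% probability to observe one or more among a small subset of 600 subjects and six or more events", the latter among 3,000 subjects. The 600 is introduced as "A small subset of 20% of all subjects" and also serves as the conservative estimate of patients available at 10 years.

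Elsewhere the size is 2,000. Section 2.3 says: "The EXCC/IBE module targets up to 2,000 patients (1,700 and 300, respectively"). Table 1 lists the same 1,700 and 300. The abstract says: "This registry will enroll approximately 3,355 adult patients".

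**The concern.** Both sizes cannot be the full enrolment of one module, and 600 is 20% of 3,000, not of 2,000. If the module is planned at 2,000, the paragraph credits it with detection and precision that belong to a sample half as large again.

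This matters because the paragraph is the only justification the article gives for the size of its largest module (2,000 of 3,355). The registry specifies no statistical hypotheses (section 2.9), so these detection and precision statements carry the sample-size rationale. A regulator or reader would take from them a better chance of seeing repeated rare events, and shorter intervals, than the planned enrolment gives.

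**Working it through.** **Inputs.** Module size 2,000 = 1,700 + 300 (section 2.3, Table 1). Registry total 3,355 (abstract). Subset fraction 20%, rare-event rate 1/350 and outcome rate 10% (section 2.8).

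**Which size does the rest of the article support?** 2,000 + 1,200 + 155 = 3,355, which is the abstract total. With 3,000 the sum would be 4,355. For the subset, 600 / 0.20 = 3,000, whereas 0.20 × 2,000 = 400.

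**Formulas.** P(at least 1) = 1 − (349/350)^n. P(at least 6) = 1 − the sum over k = 0 to 5 of the binomial(n, 1/350) probabilities. Exact (Clopper-Pearson) 95% length with x = 0.10n: Beta(0.975; x+1, n−x) − Beta(0.025; x, n−x+1).

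**Results.** The plan's own sizes come first in each pair.

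| Quantity | Stated | n used in the text | n from the 2,000 target |
|---|---|---|---|
| P(at least 1), subset | >80% | 600: 1 − (349/350)^600 = 82.0% | 400: 1 − (349/350)^400 = 68.2% |
| P(at least 6), full | >80% | 3,000: 85.6% | 2,000: 50.8% |
| Exact CI length at 10%, full | 2.2% | 3,000 (x = 300): 2.18% | 2,000 (x = 200): 2.68% |
| Exact CI length at 10%, subset | 5.0% | 600 (x = 60): 4.97% | 400 (x = 40): 6.13% |

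All four stated figures reproduce at 3,000 and 600. The choice of interval method does not change the conclusion: Wald lengths at 2,000 and 400 are 2.63% and 5.88%.

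**What 2,000 and 400 do support.**
- At 2,000 and 1/350: at least one event 99.7%, four or more 82.2%, five or more 67.5%. Four or more is therefore the largest count with probability above 80%.
- At 400: solving 1 − (1 − p)^400 = 0.80 gives p of about 1/249. A rate of 1/245 gives 1 − (244/245)^400 = 80.5%.

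**The power sentence.** Its test and alpha are not stated, so I assume a one-sample, two-sided 5% test: power = Φ[(|p0 − p1| − 1.96·√(p0(1−p0)/n)) / √(p1(1−p1)/n)].
- n = 2,000, p0 = 10%, p1 = 8.5%: (0.015 − 1.96 × 0.006708) / 0.006236 = 0.297, so power is 61.7%. With p0 = 8.5% and p1 = 10% it is 66.1%.
- n = 3,000: 79.9% and 82.0% respectively.
- Other readings at 2,000: one-sided 5% one-sample tests give 73.8% and 76.0%; two-sample comparisons give 50% or less.

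So the stated 80% fits 3,000 under this assumption, although the text attaches it to 2,000. The CTAG-AC and TBE figures in the same section reproduce at their own targets to within about 0.1 percentage point, so the mismatch is confined to the EXCC/IBE paragraph.

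**The case against.** Each figure is correct for the n printed beside it, and the registry tests no hypothesis, so no success criterion rests on these numbers. The paragraph starts from a 10% rate, "established based on an assumed outcome rate 10%, which is on the scale of expected endoleak", and at that rate the loss is modest: about 0.5 points of interval length overall and 1.1 in the subset. The 20% is only a chosen conservative fraction. If n = 600 is kept, both 600-based figures stand. Those points hold, and they limit the finding.

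They also rule out stronger readings. A reader might infer that the registry is likely to miss 1/350 events altogether. It is not: at 2,000 the chance of at least one is 99.7%, and what fails overall is the count of six or more. A reader might also infer that every figure for the module is wrong. Only the two 3,000-based figures fail whichever way the subset is settled; the 600-based ones fail only if the 20% is what is kept. Nor is the lack of separate precision lines for EXCC and IBE an error, because the section sizes the module as a whole with a generic subset.

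What the objection does not remove is the contradiction. Two full sample sizes are given for one module, and nothing outside this paragraph supports 3,000.

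**Conclusion.** The inconsistency is real and rests on the article's own numbers. With the module at 2,000, the probability of six or more events at 1/350 is 51%, not above 80%, and the exact 95% interval at 10% is 2.7 points long, not 2.2. If the 20% subset is also kept (n = 400), the probability of at least one event is 68%, not above 80%, and the interval is 6.1 points long, not 5.0. Section 2.3 words 2,000 as an upper target, so smaller enrolment would do no better.

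The detection and interval results assume only binomial sampling and the stated rates. The power result is conditional: about 62–66% at 2,000 against 80–82% at 3,000, if the test is one-sample and two-sided at 5%. It is tempting to say outright that the 80% power is wrong. The article does not name the test or alpha, so it supports only a recheck. The pattern is consistent with a paragraph calculated for 3,000 in which one number was later changed, but the article does not show that.

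**What to change.** Settle the module size, then make the whole paragraph agree with it.

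- **If 2,000 is the target:** replace 3,000 by 2,000 and the subset by 400. State a more than 80% chance of at least one event of rarity 1/245 among 400, and of four or more of rarity 1/350 among 2,000. Give exact 95% interval lengths of 2.7% and 6.1% at a 10% rate. If 600 is preferred as the subset, label it 30% of 2,000 and keep its two figures.
- **Power sentence:** name the test and alpha and recompute at the chosen size. Correcting the other figures alone would leave this one doubtful.
- **If 3,000 is the target:** correct section 2.3, Table 1, the abstract total and the 2,000 in the power sentence.

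Separate lines for EXCC (1,700) and IBE (300) are optional. With 2,000 the cost is a text correction with somewhat less favourable figures. With 3,000 the published enrolment target itself changes, which is more than wording.

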### Statistical analysis

2.9

As a real-world registry, no statistical hypotheses are specified. By default, statistical testing will test for two-sided differences across arbitrary subgroups to better understand clinical outcomes. All data will be included in their appropriate analysis as intention to treat.

Statistical analyses will employ a combination of descriptive and inferential methodologies to ensure comprehensive evaluation of patient outcomes. Kaplan–Meier survival analyses estimate freedom from mortality, reintervention, and major adverse events over time. Cox proportional hazards models will be used to identify predictors of device failure and clinical complications, while multivariate regression models assess the influence of patient demographics, procedural variables, and anatomical characteristics on long-term outcomes. To provide contextual comparisons, the registry integrates historical data from prior observational studies, allowing for benchmarking of device performance against established clinical standards.

The contrast-enhanced computed tomography (CT) component of this study provides a robust foundation for quantitative imaging analysis and potential future applications of machine learning. Contrast CT offers high spatial and temporal resolution that enables precise assessment of vascular anatomy, device positioning, and procedural outcomes. Beyond its immediate diagnostic and procedural value, the imaging dataset has been structured to support the extraction of radiomic and morphological features that could inform predictive modeling. This framework allows for future implementation of advanced analytical approaches, including machine learning-based image analysis, to identify subtle imaging biomarkers and optimize outcome prediction in endovascular interventions.

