### Follow-up and clinical outcomes assessment

2.7

The registry evaluates a range of clinical and device-related outcomes, categorized as primary and secondary measures (Table 4). The primary outcomes of interest include technical deployment success, all-cause and lesion-related mortality, and device-related adverse events such as endoleaks, device migration, loss of branch patency, renal function deterioration, and neurological complications, including stroke, paraplegia, and paraparesis (Table 4). Secondary outcomes are device specific and encompass access-related complications, new-onset renal failure, false lumen remodeling in TEVAR-related registries, and health economic parameters, including hospital length of stay and ICU admission rates, depending on the module. Additionally, the EXCC/IBE module assesses quality of life measures, using the EQ-5D-5L, a validated instrument available in over 150 language versions through the EuroQol Research Foundation, ensuring applicability across the registry's geographically diverse participating centers (10, 11), incidence of erectile dysfunction, and buttock claudication as part of long-term follow-up.

**Table 4 T4:** Primary and secondary outcomes for each module.

Primary Outcomes		
• Deployment Technical Success (index procedure only)^a^ Assessment of the following through all follow-up windows (unless indicated) ○ Mortality (all-cause, lesion-related) ○ Device and Treatment-related Adverse Events (AEs), including: ▪ Lesion rupture (treated area) ▪ Lesion enlargement (treated area) ▪ Endoleaks ▪ Device migration ▪ Loss of aortic/branch patency ▪ New onset renal failure (w/in 30 days of the procedure) ▪ Renal function deterioration ○ Serious Adverse Events (SAEs) ○ AEs with unknown causal relationships ○ Device integrity events (e.g., fracture, kinking, compression) ○ Reintervention		

Secondary Outcomes		
AA Module	TA Module	TB Module

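### Kaplan-Meier is the only estimator named for freedom from reintervention over 10 years; with deaths censored, its complement overstates the proportion of patients who have the event

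*Protocol article*

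**What the plan says.** Section 2.9 (Statistical analysis) states that Kaplan-Meier "survival analyses estimate freedom from mortality, reintervention, and major adverse events over time". For regression it says that "Cox proportional hazards models will be used to identify predictors of device failure and clinical complications". It also plans tests across subgroups and benchmarking against historical data. No cumulative incidence or other competing-risk method is named anywhere in the article, and the handling of deaths in the non-fatal analyses is not stated.

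Table 4 (section 2.7) lists "Mortality (all-cause, lesion-related") as primary outcomes, apart from reintervention and the individual device events. Section 2.3 says that the EXCC/IBE and CTAG-AC "modules follow patients for ten years post-procedure, whereas the TBE module has a follow-up period of two years". Section 2.8 describes "A small subset of 20% of all subjects" in EXCC/IBE, and 120 of 1,200 in CTAG-AC (there called the TA module), as both an illustrative subgroup size and "a conservative estimate of subjects available at 10 years". The limitations (section 3.1) discuss attrition and loss to follow-up, but not death as a competing event.

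**The concern.** Kaplan-Meier suits all-cause mortality. For reintervention, a patient who dies can no longer have the event. Censoring that patient at death treats him or her as still able to have it later, at the same rate as the survivors. 1-KM then estimates what would happen if nobody died, not the share of treated patients who undergo reintervention. The other option, counting deaths as events, gives reintervention-free survival, which is not a reintervention rate either.

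Reintervention is a primary outcome, the registry's stated aim is real-world outcomes, and section 2.10 plans publications through year 10. The two 10-year modules hold 1,700 + 300 + 1,200 = 3,200 of the 3,355 planned patients. A 10-year Kaplan-Meier figure read as absolute patient risk would be too high, and the excess grows with follow-up.

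**Working it through.** **Inputs from the article.** Estimator: Kaplan-Meier (2.9). Horizons: 10 years and, for TBE, 2 years (2.3). Planning outcome rate: 10% (2.8). Planned precision for CTAG-AC: exact 95% interval width 3.5% at P = 10%, N = 1,200 (2.8).

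**Assumptions.** The article gives no mortality or reintervention rate, so 10-year mortality m is varied from 20% to 80%. Hazards are constant and the times to event and to death are independent.

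**Step 1: the plan's own figure.** The Clopper-Pearson width at P = 10%, N = 1,200 is 3.48%, which agrees with the stated 3.5%. The half-width, about 1.7 points, serves as a yardstick for the bias.

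**Step 2: formulas.** Let Le and Ld be the cumulative hazards of event and death to 10 years.
- With deaths censored: 1-KM = 1 - exp(-Le). A Kaplan-Meier rate of 10% gives Le = -ln(0.90) = 0.105.
- Death: Ld = -ln(1 - m).
- Cumulative incidence: CIF = Le/(Le + Ld) x [1 - exp(-(Le + Ld))].

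At m = 50%: Ld = 0.693, so CIF = 0.105/0.799 x (1 - 0.90 x 0.50) = 0.132 x 0.55 = 7.3%.

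**Step 3: range at 10 years.**

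| Assumed mortality | CIF when 1-KM = 10% | Gap (points) | Ratio | CIF when 1-KM = 20% |
|---|---|---|---|---|
| 20% | 9.0% | 1.0 | 1.11 | 18.0% |
| 30% | 8.4% | 1.6 | 1.19 | 16.9% |
| 50% | 7.3% | 2.7 | 1.38 | 14.6% |
| 70% | 5.9% | 4.1 | 1.70 | 11.9% |
| 80% | 5.0% | 5.0 | 1.98 | 10.2% |

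**Step 4: front-loaded events.** If half of the 10-year cumulative event hazard falls in year 1, a 10% Kaplan-Meier rate corresponds to 9.1%, 8.3% or 7.5% at 30%, 50% or 70% mortality (ratio 1.10 to 1.34). Early events leave less room for death to intervene, so the bias shrinks but keeps its sign.

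**Step 5: TBE at 2 years.** Over the same mortality range, with constant hazards that give a 10-year 1-KM of 10% to 30%, the gap at 2 years is at most 1.0 point. At 50% 10-year mortality it is at most 0.5 point.

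**Step 6: against planned precision.** At 50% mortality the gap is 1.7 points (front-loaded) to 2.7 points (constant hazards), which equals or exceeds the 1.7-point half-width. That half-width belongs to the full 1,200. With only 120 patients the stated width is 11.5%, a half-width of about 5.8 points, so an actual 10-year estimate will be less precise than the yardstick suggests.

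**Step 7: what mortality does to comparisons.** Fix reintervention at an assumed 2% per year.
- 1-KM at 10 years = 1 - exp(-0.20) = 18.1%, whatever the death rate.
- CIF with death at 5% per year = 0.02/0.07 x (1 - exp(-0.70)) = 14.4%.
- CIF with death at 12% per year = 0.02/0.14 x (1 - exp(-1.40)) = 10.8%.

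Here it is the cumulative incidence, not Kaplan-Meier, that moves with background mortality.

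**The case against.** The strongest reply is that absolute patient risk and device performance are two different estimands, and Kaplan-Meier is defensible for the second. Section 2.9 gives benchmarking of devices as a purpose. Under independent censoring, a curve that does not shift with background mortality serves that purpose, as step 7 shows. This stands. A reader might infer that Kaplan-Meier distorts comparisons between modules, regions or historical series with different mortality, and that Gray's test should replace the log-rank test. The arithmetic points the other way: groups with identical reintervention hazards but different mortality differ in cumulative incidence, and Gray's test would be sensitive to that.

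A reader might also infer heavy mortality from the 20% and 10% availability figures. The article does not support this. Both figures are called conservative, both double as subgroup sizes, and neither separates death from other loss. Nor does the article call the 10-year rate its principal regulatory output; the abstract's conclusion speaks of mid-term outcomes, and the named publication milestones end at 1 year, with later reporting described only in general terms.

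Two further points stand in part. The term major adverse events is undefined; a composite that includes all-cause death is not biased in this way. And section 2.9 is a summary, so the full plan may specify how deaths are handled or add cumulative incidence. But the article does name an estimator for reintervention, and neither way of handling deaths in it yields the real-world reintervention proportion. The hypothetical no-deaths estimand that would justify censoring is not stated.

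**Conclusion.** The point holds, limited to absolute risk. If deaths are censored, 1-KM for reintervention exceeds the proportion of treated patients who have the event; the direction is certain whenever some patients die before the event. The size cannot be derived from the article. Under assumed 10-year mortality of 20% to 80%, independence and constant hazards, the ratio at a 10% Kaplan-Meier rate runs from 1.11 to 1.98; front-loading lowers it to 1.10 to 1.34 over 30% to 70% mortality. This can matter for EXCC/IBE and CTAG-AC at 10 years and is small for TBE at 2 years. It applies to lesion-related mortality in the same way, with other-cause death competing, and to major adverse events only if the term excludes all-cause death. The Cox models are not in question: read as cause-specific hazards, they are sound. This is a worthwhile correction to the analysis wording and does not call the registry's design into question.

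**What to change.** In section 2.9 and the analysis plan:
- Keep Kaplan-Meier for all-cause mortality.
- For reintervention, lesion-related mortality and non-fatal events, report Aalen-Johansen cumulative incidence as the absolute-risk estimate, with death (other-cause death for lesion-related mortality) as the competing event.
- Compare groups and benchmark device performance on cause-specific hazards (log-rank or Cox), not on Gray's test alone.
- Keep Kaplan-Meier freedom-from curves as a labelled display for comparison with historical series, stating that deaths are censored.
- Say whether major adverse events include all-cause death.

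Mortality and reintervention are already collected, so the cost is revised wording and standard code. The downside is two displays instead of one. The change does not address loss to follow-up other than death, which cumulative incidence still assumes to be non-informative.
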